## Abstract

**Background:**

The therapeutic use of intermittent theta burst stimulation (iTBS) delivered to the left dorsolateral prefrontal cortex (LDLPFC) is a relatively new but promising treatment option for depression. There is a need for more knowledge on the mechanisms involved in its antidepressant effects.

**Methods:**

This is a single-centre, prospective, randomized, double-blind, placebo-controlled trial with two arms, iTBS and sham iTBS. Adult outpatients with unipolar major depressive disorder of at least moderate severity will undergo cognitive assessment with an N-back task (0-back and 2-back), functional and structural magnetic resonance imaging and assessment of depression severity before and after brain stimulation. Neuronavigated iTBS or sham stimulation will be targeted at the LDPFC once a day for 10 consecutive workdays. ITBS will be delivered with the parameters 120% of resting motor threshold, triplet 50 Hz bursts repeated at 5 Hz; 2 s on and 8 s off, 600 pulses per session with a total duration of 3 min 9 s. The severity of depression will be measured with the Montogomery Aasberg Depression Rating Scale and the Beck Depression Inventory – second edition.

In the iTBS group relative to sham, we expect significant antidepressant effects and improved N-back performance, associated with increased integrity in white matter tracts functionally connected with the LDLPFC and emotion regulation areas within the rostral anterior cingulate cortices, alongside potential increases in cortical thickness in these regions. On functional imaging, we expect to observe increased brain activity in the LDPFC during the performance of the N-back condition with higher cognitive load (2-back) in the iTBS group relative to sham.

**Discussion:**

iTBS is a promising, time-efficient, and considered a safe treatment option for depression according to existing evidence. This trial aims to assess the neurocognitive impact of a 2-week, once-daily iTBS compared to sham iTBS, targeting the LDLPFC in depressed adult outpatients. The study investigates the relationships between changes in cerebral measures and cognitive performance on an N-back task in relation to the antidepressant effect following iTBS. This trial delves into the neurocognitive mechanisms of iTBS in depression, potentially offering novel scientific insights into its treatment effects and mechanisms of action.

**Trial registration:**

ClinicalTrials.gov NCT06534684. Retrospectively registered on August 1st 2024.

## Administrative information

Note: the numbers in curly brackets in this protocol refer to SPIRIT checklist item numbers. The order of the items has been modified to group similar items (see http://www.equator-network.org/reporting-guidelines/spirit-2013-statement-defining-standard-protocol-items-for-clinical-trials/).

## Introduction

### Background and rationale {6a}

Depressive disorders impose substantial societal and economic burdens, with conventional treatments often inadequate for many patients, underscoring the necessity to explore alternative therapeutic strategies [1, 2]. Non-invasive brain stimulation techniques, such as intermittent theta burst stimulation (iTBS) have emerged as promising interventions for depressive disorders, with the potential for cognitive improvement in addition to antidepressant effects [3–5]. This is important because cognitive dysfunction is involved in impaired functioning in depression and is associated with lack of remission and relapse [6].

iTBS, a modified form of high-frequency repetitive transcranial magnetic stimulation (HF rTMS), delivers targeted magnetic field pulses, inducing enduring changes in brain activity. Unlike the HF-rTMS sessions lasting approximately 20–40 min, iTBS protocols for depression are significantly shorter, lasting only about 3 min, thus offering reduced stimulation duration and enhanced patient comfort while maintaining therapeutic efficacy. The treatment is reported to be well-tolerated with only mild side effects [7–10].

In therapeutic use for depression, excitatory paradigms with rTMS or iTBS are most often targeted at the left dorsolateral prefrontal cortex (LDPFC) [11]. It is believed that the antidepressant mechanism of action involves a normalization of imbalanced activation patterns in the prefrontal cortex of depressed individuals [12]. iTBS operates through rapid bursts of pulses delivered at a frequency of 50 Hz, mimicking the brain’s theta rhythm [13]. This rhythm is associated with long-term potentiation and enduring brain changes primarily in the medial part of the prefrontal cortex (including the anterior cingulate cortex), regarded as important brain correlates of cognitive control processes [5]. Hence, iTBS has been hypothesized to improve cognitive control functions in depression alongside amelioration of mood symptoms [14].

However, much remains unknown about the antidepressant mechanisms of action of iTBS and the neurocognitive changes induced by iTBS [15]. Hence, this trial aims to assess the effect of iTBS targeted to the LDLPFC on improvements in frontal lobe function in depression. Previous studies on cerebral anatomical changes after TMS in depression have not used the iTBS protocol. Nevertheless, using 10 Hz rTMS Boes et al. [16] found that the rostral cingulate cortex increased in thickness following traditional rTMS treatment and that the cerebral thickness of this area before starting treatment was a marker for treatment response. Regarding white matter structural changes, prior studies have implicated decreased fractional anisotropy (FA) in white matter tracts, more specifically in the uncinate fasciculus and in the cingulum bundle, as a characteristic of major depression. Using traditional rTMS, FA has shown to increase in depressed patients. First, FA increase was shown in the left middle frontal gyrus and the change correlated with the decrease in depressive symptoms [17]. Furthermore, Tateishi et al. [18] found increased white matter integrity after rTMS in depressed patients, as well as improvements on neurocognitive tests. However, neurocognitive improvement was not correlated to FA increase [18]. To our knowledge, there are no studies examining similar structural changes in depressed brains following iTBS. Moreover, it is conceivable that iTBS may improve neurocognitive functions, given the crucial role of the frontal cortices for cognition in general, and executive functions (EF) specifically. The N-back task is frequently utilized to assess working memory (WM) and EF deficits [19]. Given the anticipated heightened neural activity in the left DLPFC induced by iTBS, employing the N-back task during brain functional magnetic resonance scanning (fMRI) could serve as a reliable indicator of this neural modulation, given its established association with DLPFC activity [19].

### Objectives {7}

The primary objectives of the present trial are to assess the impact of a 2-week, once-a-day application of iTBS over the LDLPFC on cerebral and N-back task performance, and to examine the associations between changes in cerebral functions, cognition, and the reduction in depression symptoms following iTBS. The underlying hypothesis posits that the reduction in scores on the Montgomery-Åsberg Depression Rating Scale (MADRS) [20] and Beck Depression Inventory-II (BDI-II) [21], will be statistically significant after the 2-week iTBS treatment in comparison to sham treatment, drawing from data reported in prior studies [8]. Although a decrease in depressive symptoms is expected in the sham group due to the placebo effects [22] we anticipate that the physiological effects of iTBS will surpass placebo responses within the parameters of the current study design [23].

Research questions and hypotheses:Does the iTBS protocol induce significant changes in the integrity of white matter cerebral tracts and are these changes related to reductions in depression and improved N-back task performance? We expect that the reduction in MADRS and BDI-II scores from baseline to the post-test will be significantly associated with changes in white matter fractional anisotropy (FA) induced by iTBS, where a larger increase in FA will show larger reductions in depressive symptoms in the iTBS group compared to the group receiving sham.Are changes in depressive symptoms and executive functions after iTBS treatment related to grey matter anatomical changes in cerebral measures? The expected larger reductions in MADRS and improved N-back task performance in the iTBS group between baseline and post-test compared to the placebo group will be significantly associated with increased thickness of the rostral anterior cingulate cortex and the LDPFC.Will iTBS treatment change the observed neural efficacy and behavioural performance to cognitive demanding tasks (N-back) in depressed patients? We expect that patients who received iTBS treatment will display significantly larger changes in functional BOLD response, with significantly higher BOLD response in the DPFC to a demanding cognitive task (2-back) during fMRI scanning compared to patients receiving sham stimulation. Larger reductions in depressive symptoms will be associated with larger changes in fMRI BOLD responses and greater improvements on the N-back task.

### Trial design {8}

This trial is a single-centre, randomized, sham-controlled, parallel-group, double-blind clinical trial. Participants will be recruited prospectively.

## Methods: participants, interventions, and outcomes

### Study setting {9}

The trial will be performed in clinical laboratories at the UIT, the Artic University of Norway, and the University Hospital of North Norway—Health Trust (UNN-HF), Tromsø, Norway. The laboratories at UIT and the UNN are located in the same campus area.

### Eligibility criteria {10}

Inclusion criteria are adult out-patients between 22–65 years of age meeting the diagnostic criteria of at least moderate depression. Fluency in the Norwegian language is required. Alongside the M.I.N.I. psychiatric interview [24], the MADRS [20] will be administrated. A MADRS score of ≥ 20, usually indicates a moderate depression. Patients must volunteer to provide informed, written consent, be able to follow the treatment schedule and have a satisfactory safety screening for iTBS and MRI. Furthermore, drug therapy must have been stable for the last 3 weeks before the first treatment day with iTBS and is to be kept stable throughout the study until close-out, 4 weeks after the last day of iTBS treatment.

Patients will be excluded from the study if the clinical interview indicates that the current depressive episode is in the mild range or triggered by grief or a recent major stressful life event, or contrary, that the current episode fulfils the criteria for a major depressive episode requiring inpatient treatment and heightened risk of suicide. Further exclusion criteria are: The clinical assessment indicates the likelihood of bipolar disorder, borderline personality disorder or psychotic symptoms, alcohol or substance abuse/addiction in the last 6 months, current eating disorders, obsessive–compulsive disorder, or post-traumatic stress disorder. Exclusion criteria due to safety issues are a medical history of seizure, neurological or neurosurgical pathologies, cardiac or systemic disease, metallic prosthetic material or foreign objects (pacemakers, prosthetic eye equipment, etc.), and being pregnant or currently breast-feeding [25, 26]. Eligibility interviews are conducted by a medical doctor or a specialist in clinical psychology.

### Who will take informed consent? {26a}

Prior to enrolment, detailed information about the study is provided, an eligibility screening (safety check, inclusion/exclusion criteria) is conducted by telephone, and the consent form is sent by e-mail. This procedure is conducted by one of the main investigators. A medical doctor is consulted in case of patient’s medications, and possible interactions with iTBS treatment. If an eligible patient still wishes to participate after this step, the written informed consent form must be handed in at the study site prior to the baseline assessments.

### Additional consent provisions for collection and use of participant data and biological specimens {26b}

All participants will donate blood samples for a biobank in a related, ongoing study with its own ethical approval and associated published protocol [23], but none of the samples will be used for studies described in the present protocol.

## Interventions

### Explanation for the choice of comparators {6b}

In this RCT, the effects of iTBS will be compared against sham iTBS. Sham iTBS resembles the active iTBS condition and provides a sensory experience that is difficult to separate from real iTBS for naïve participants. The use of a placebo treatment will allow us to separate the effect of iTBS from other non-iTBS-specific factors.

### Intervention description {11a}

Theta burst stimulation will be performed with a Mag & More PowerMag EEG 100 system (https://magandmore.com) with a double PMD70 p-cool figure-of-eight coil. Sham stimulation will be performed by the double PMD70 p-cool figure-of-eight coil Sham system. The sham system has an identical look, weight and sound compared to the active coil, and delivers electrical stimulation that can be felt at the skin but without penetrating the skull. Resting-motor threshold (RMT) will be determined prior to stimulation in accordance with the consensus guidelines for rTMS [21]. ITBS will be delivered with the same parameters as in Blumberger et al., [8]: 120% RMT triplet 50 Hz bursts repeated at 5 Hz; 2 s on and 8 s off, 600 pulses per session with a total duration of 3 min 9 s. Treatment will be provided for 10 days for two consecutive weeks (except Saturdays and Sundays). Before the first treatment, participants will perform MRI examinations (T1, DTI, fMRI) and the high-resolution T1-weighted obtained at that point will be used for real-time MRI-guided neuro-navigation for optimal coil positioning. A Localite TMS-navigator system (https://www.localite.de) will be used for the determination of the target area within the DLPFC. The Localite system visualizes the patient’s brain on a pc-screen based on the T1 images, and the coil is connected to the Localite system making it possible to move the coil over the desired brain structure and correctly position it. The target MNI coordinate will be *x* − 38, *y* + 44, *z* + 26, based on the findings of Fox et al. [12] who identified this point based on clinical outcomes and whole-brain functional connectivity for rTMS studies.

### Criteria for discontinuing or modifying allocated interventions {11b}

The criteria for discontinuing or modifying allocated interventions for a given participant include the following: worsening of disease, report of adverse side effects, withdrawal of consent, change in drugs or not receiving stimulation on more than 2 days. If the patient is absent from one or two stimulations, these will be added to the treatment schedule. For safety reasons, participants will be asked about sleep, alcohol, illegal drugs and medication use prior to each simulation. Participants will be asked about their well-being prior to and after each iTBS stimulation. The participants will be asked to drink no more than one unit of alcohol the night before stimulation. If the patient reports drinking more alcohol, stimulation will be postponed to the day after. Stimulation will also be postponed if the participant reports significant tiredness and/or lack of sleep the night before [23].

### Strategies to improve adherence to interventions {11c}

Patients are carefully informed about the requirements for participation prior to study enrolment. During participation, they are cared for by the study nurses on a day-to-day basis. A clinical psychologist assesses the patient’s well-being after five stimulations.

### Relevant concomitant care permitted or prohibited during the trial {11d}

No treatments are prohibited during the trial, but drug therapy must have been stable for the last 3 weeks prior to the first treatment day with iTBS and must be kept stable throughout the study until 4 weeks after the last day of iTBS treatment. All concurrent treatments will be recorded [23].

### Provisions for post-trial care {30}

A total of ten sessions of once-a-day iTBS is offered to a patient who has received placebo and still meets the inclusion criteria at the time of disclosure of allocation.

### Outcomes {12}

The primary outcome measures of this trial are cerebral changes and their association with changes in depressive symptoms and cognitive performance on the N-back task after 2 weeks of daily iTBS or sham iTBS.

Participants will undergo brain imaging prior to and after the iTBS or sham protocol. T1-weighted anatomical cerebral MRI images will be obtained for measures of cortical volume and thickness. Diffusion tensor imaging (DTI) will be used to get data for white matter integrity, whereas fMRI data will be used to obtain functional blood-oxygen-level-dependent (BOLD) data for responses to the N-back task during scanning.

Change in level of depression in measured pre and post-stimulation with the semi-structured clinician-led patient interview MADRS [20] and with the patient-reported BDI-II [21]. Based on the data from Blumberger et al. [8], we estimate a mean decrease of approx. 25% in depressive symptoms over a 2-week treatment course in those receiving iTBS. The minimal clinically important difference (MCID) for BDI-II is suggested to be 17.5% change from baseline and 13% change for the MADRS [27].

Between-group change in working memory and executive functions is measured with performance on a N-back task prior to and after stimulation. The N-back task can be performed on a laptop prior to and after the iTBS stimulation protocol and it is also implemented for use in fMRI [28] We will use 0-back and 2-back tasks that generate measures of the number of correct responses, reaction time, commission and omission errors.

### Participant timeline {13}

Figure 1 shows the schedule of enrolment, interventions and assessments.

**Fig. 1 Fig1:**
[figure not shown]
Schedule of enrolment, interventions and assessments. *A*bbreviations: *M.I.N.I* Mini International Neuropsychiatric Interview, *MADRS* Montgomery and Asberg Depression Rating Scale, *fMR*I functional magnetic resonance imaging

### Sample size {14}

To date, only a single study has examined the relation between fractional anisotropy (FA) and iTBS [29], however, that study tested the after-effects of iTBS in the primary motor cortex and included only healthy participants. To our knowledge, there are no studies to date that have examined the change in FA after iTBS treatment. Furthermore, there are to our knowledge no previous studies that have measured the change in cortical thickness after iTBS treatment. Due to the lack of previous studies investigating changes in functional and structural cerebral measures after iTBS treatment in depressed patients, we based the sample size calculation on the expected cognitive improvement in N-back performance during fMRI. For the fMRI measures using the N-back task, we expect similar effect sizes as in previous comparable studies (summarized in [28]), where moderate to large effect sizes and significant group differences were observed with group sizes of 20–30 participants when using the same N-back stimuli as we do. Based on previous data [28] for N-back changes in fMRI, in a repeated analysis (*F*-test), medium effect size (*f* = 0.25), two groups, alpha = 0.05, and power = 0.90, correlation between repeated measures = 0.5, sphericity correction = 1, the required sample size is 46 for the fMRI analyses, with equivalent group sizes of iTBS and sham. There is limited information about drop-out rates for iTBS treatment, however, a meta-analysis on rTMS [30] suggested the mean drop-out rate to be between 7 and 8%. Thus, assuming a total drop-out of 10%, the present study must include a total of 50 participants.

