## Statistical methods

### Statistical methods for primary and secondary outcomes {20a}

Repeated measures data will be analysed by linear mixed models (LMM) which allow for a combination of fixed and random effects. LMM estimates the parameters using all available patient data and is thus less sensitive to scattered missing data, and has flexible modelling options for the covariance structure of the data [41]. Single means (e.g. baseline data) will be analysed with statistical methods within the framework of general linear models (GLM), if the statistical assumptions for GLMs are met. In case of non-normal data, non-parametric statistics will be performed. SPSS and R will be used for statistical analyses of clinical and cognitive data. Analyses of brain imaging data will be performed in separate programs according to the type of data. FreeSurfer (FS) (https://surfer.nmr.mgh.harvard.edu/) will be used for preprocessing of structural imaging data (volumetric analyses and segmentation), and Tracula inbuilt in FS will be used for DTI data [42], and Permutation Analysis of Linear Models (PALM) will be used to perform statistics on structural data preprocessed in FS, and in analyses where imaging data is combined with other data as covariates or factors [43]. SPM12 (https://www.fil.ion.ucl.ac.uk/spm/software/spm12/) will be used for preprocessing of fMRI data. An alpha value of 0.05 will be used for all analyses, and Bonferroni-corrections will be applied when appropriate for controlling the type-1 error rate.

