## Discussion

The present study protocol outlines the scientific rationale for a randomized, double-blind, parallel-group, sham-controlled neuroimaging trial. This trial aims to investigate the neurocognitive effects of intermittent theta burst stimulation (iTBS) on unipolar depression in patients referred to the psychiatric outpatient clinic at the University Hospital of North Norway.

Understanding the neurocognitive changes induced by iTBS is crucial for several reasons: first, to elucidate the mechanisms underlying iTBS; second, to determine how cerebral changes after iTBS relate to cognitive and antidepressant outcomes post-treatment and third; to inform patient selection for a therapy that holds promise for improvement of cognitive control functions in depression.

To date, few studies have assessed how iTBS affects cerebral grey or white matter structural integrity through pre- and post-treatment MRI examinations. This neuroimaging study boasts several strengths, including a placebo control and a relatively large sample size.

The study has the potential to provide novel scientific insights into the treatment effects of iTBS, a promising and currently considered safe treatment option for depression. Furthermore, it will be among the few studies to elucidate the neurocognitive mechanisms of iTBS and its potential to enhance neurocognitive function in depression.

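### The 90% power claimed for a medium effect (f = 0.25) is power for a 1.0 SD between-group difference in change; a conventional medium difference of 0.5 SD has about 38% power

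*Protocol article*

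**What the plan says.** The protocol article, Sample size {14}, bases the trial's size on the N-back task during fMRI. It describes the test only as "in a repeated analysis (*F*-test", sets the effect as "medium effect size (*f* = 0.25", and continues with "two groups, alpha = 0.05, and power = 0.90, correlation between repeated measures = 0.5, sphericity correction = 1, the required sample size is 46". The 46 are evaluable participants in two equal groups, raised to 50 for drop-out. The section does not state the number of measurements, does not say which term of the repeated-measures model is tested, and does not convert f into a difference in change. It says that earlier studies with the same stimuli found moderate to large effects with groups of 20 to 30.

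Two other sections supply what is left open. Objectives {7} asks whether the change under iTBS exceeds the change under sham, for the BOLD response in particular. The data collection section {18a} gives two in-scanner N-back sessions, one before and one after treatment.

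**The concern.** For two equal groups compared on a mean, f is half the standardised difference, so f = 0.25 means 0.5 SD, which is the conventional medium effect. A reader who sees f = 0.25 beside that label will take the trial to have 90% power for a difference of about half a standard deviation between iTBS and sham. In a two-group, two-occasion interaction the same f stands for a difference in change twice as large. This is the only sample-size justification in the article, so the sensitivity it states is the one readers will carry to the results.

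**Working it through.** **Inputs.** From Sample size {14}: f = 0.25, k = 2 groups, alpha = 0.05, power 0.90, correlation rho = 0.5, sphericity correction 1, N = 46 (23 per arm). From the data collection section {18a}: m = 2 in-scanner measurements. From Objectives {7}: the contrast of interest is the between-group difference in pre-post change. Assumption: the tested term is the group-by-time interaction.

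**Step 1: reproduce 46.** Noncentrality lambda = f² × N × m / (1 − rho) = 0.0625 × N × 2 / 0.5 = 0.25N, with df1 = 1 and df2 = N − 2.
- N = 44: lambda = 11.0, power 0.8997.
- N = 46: lambda = 11.5, power 0.912.

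So 46 is the smallest even N that reaches 90%. Three measurements would give 36, four would give 30, and the between-groups main effect would give 130. The time main effect also gives 46, so the number alone does not show which within-subject term was meant.

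**Step 2: what f = 0.25 means for the interaction.** Let the arms be equal at baseline and let the difference in change be delta, so the cell means are 0 and delta in one arm and 0 and 0 in the other. The interaction component in each of the four cells is plus or minus delta/4. Hence f = delta / (4 × sigma), and delta = 4 × 0.25 × sigma = 1.0 sigma, where sigma is the SD of a single measurement.

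The SD of change is sigma × √(2(1 − rho)) = sigma × √1 = 1.0 sigma at rho = 0.5. The assumed effect is therefore 1.0 SD on both the raw and the change-score scale.

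Cross-check: a two-sample t-test on change with d = 1.0 and 23 per arm has lambda = d² × 23/2 = 11.5 and power 0.912, identical to step 1. A simulation with 40,000 runs gave 0.913.

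**Step 3: power at smaller differences, N = 46, rho = 0.5.** Change scores: lambda = d² × 23/2, df2 = 44. Baseline-adjusted: the residual variance is (1 − rho²) = 0.75 of the raw variance, so lambda = d² × 23 / (2 × 0.75), df2 = 43.

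| Difference (raw SD) | lambda, change | Power, change | lambda, adjusted | Power, adjusted |
|---|---|---|---|---|
| 1.0 | 11.5 | 0.91 | 15.33 | 0.97 |
| 0.8 | 7.36 | 0.76 | 9.81 | 0.86 |
| 0.5 | 2.875 | 0.38 | 3.83 | 0.48 |

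Simulated power at 0.5 SD on change scores was 0.382. In the step 1 formula a 0.5 SD difference corresponds to f = 0.5/4 = 0.125.

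**Step 4: sensitivity to rho.** With 23 per arm, the difference detectable with 90% power is 0.977 SD of the change score. In raw SD this is 0.977 × √(2(1 − rho)):

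| rho | Raw-SD difference at 90% power |
|---|---|
| 0.3 | 1.16 |
| 0.5 | 0.98 |
| 0.7 | 0.76 |
| 0.8 | 0.62 |

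With baseline adjustment at rho = 0.5 it is 0.977 × √0.75 = 0.85.

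**The case against.** The best reply is that nothing is miscalculated: f = 0.25 carries its usual label, the section never mentions 0.5 SD, and the printed inputs let a careful reader make the conversion. The first part stands, and this should not be called an arithmetic error. But the label is what tells readers how sensitive the trial is, and on this scale it describes an effect half the size of the one used.

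Three further objections narrow the figures without restoring the claim.
- The tested term is inferred. If the time main effect was entered, N is still 46, but the calculation then does not test iTBS against sham at all.
- The statistical methods section plans linear mixed models, not a t-test on change, and does not say how baseline enters. Adjustment raises power at 0.5 SD only to about 48%.
- A higher correlation helps, but even at 0.8 the difference detectable with 90% power is 0.62 SD, and 0.5 is the plan's own value.

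It is also fair to say that the earlier data behind f cannot be seen here. An effect of 1.0 SD may be realistic, so 38% should not be presented as the power for the effect the investigators expect.

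A reader might also object to the Discussion's claim of strengths "including a placebo control and a relatively large sample size". That remark follows a comment on how few earlier studies exist and reads as relative to them. It is not a power claim, and it cannot be refuted from this document.

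**Conclusion.** The concern holds as a mislabelled sensitivity. With 46 evaluable participants the design has about 91% power for a 1.0 SD difference in pre-post change. For a conventional medium difference of 0.5 SD it has about 38% on change scores, or about 48% with baseline adjustment. At 0.8 SD the figures are about 76% and 86%. These rest on the interaction being the tested term, two measurements, 23 evaluable per arm, two-sided alpha of 0.05 and rho = 0.5. The size of the gap in raw SD depends on rho.

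Stronger readings are tempting but unsupported:
- That only a very large effect could be found. Power at 0.8 SD is already about three in four.
- That the trial would treat a null result as excluding a medium effect. No section proposes that inference.
- That the trial must be enlarged. The section cites moderate to large effects from earlier studies, and whether 1.0 SD is plausible cannot be judged without them.

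**What to change.** In Sample size {14}, name the test as the group-by-time interaction with two measurements, delete the word medium, and give the sensitivity in units of change. Suggested text:

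*With 46 evaluable participants (23 per group), two measurements, a correlation of 0.5 and two-sided alpha of 0.05, the group-by-time interaction has about 91% power for a between-group difference in pre-post change of 1.0 SD (f = 0.25), about 76% for 0.8 SD and about 38% for 0.5 SD.*

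If the planned model adjusts for baseline, say so and give the higher figures instead (about 97%, 86% and 48%). If the time main effect was the term entered, the section should say that the calculation has been restated for the interaction.

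This is a change of wording only. Enrolment, design, outcomes and analysis stay as they are. The cost is a less favourable stated sensitivity.
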